### Analysis of the Primary Aim

The primary pre-planned analyses are to examine SBP and DBP separately; however, if the two variables are correlated, MANOVA will be used to test the hypothesis that those assigned to MINT-TLC will, on average, exhibit greater 6-month decreases in SBP and DBP than those assigned to the UC condition. A mixed (fixed and random) effects model using SAS Proc Mixed is the method planned for use. Such models permit modeling heterogeneous group variances and serial correlations over time as well as the design effects of clustering. Moreover, the use of the missing data algorithms within the mixed procedure permits the inclusion of all individuals with at least one wave of data. The primary test concerns the Group × Time interaction, and the resulting F-test will provide the primary "intent-to-treat" test of the hypothesis. If this is statistically significant at the two-tailed α = 0.05 level, the magnitude of the treatment effect will be estimated with 95% Confidence Interval (CI), separately for SBP and DBP. The expectation is that the randomization of patients to treatment arm and the absence of significant selection and/or attrition biases will obviate the need for any covariates in the analysis. This has been the normative experience of the data coordinating center in over 100 randomized trials. However, in the unlikely event that imbalances are identified, propensity score analyses or other methods will be used to condition on the covariates. The predicted values of those analyses will be included as covariates together with the group by covariate interactions in the model. This procedure is most often applied in quasi-experimental and observational studies.

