**Discussion:**

This vanguard trial will provide information on how to refine MINT-TLC and integrate it into a standard treatment protocol for hypertensive African Americans as a result of the data obtained; thus maximizing the likelihood of its translation into clinical practice.

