Based on our own clinical experience and estimates from other clinical trials in uncontrolled hypertensive patients,[16-18,20,53-57] we estimate that the cross-sectional standard deviations (SD) of SBP and DBP at baseline will be about 15/12 mm Hg. It was assumed that the SD at follow-up will be as much as 25% larger in the MINT-TLC group, and that the correlation between baseline and follow-up BPs will be 0.6 in the UC group and 0.4 in the MINT-TLC group (possibly as a result of heterogeneity of treatment response). Design effects of patients clustered within physicians has been found to be minimal in our experience; for example the intracluster correlation coefficient (ICC) was estimated to be 0.02 or less, and cluster sizes are relatively small. Clustering results in reduction in power and increased requirements for sample size. The variance inflation factor (VIF) used in power calculations involving clustering depends on the size of the cluster (number of patients treated by each physician) and ICC. Power calculations were examined in sensitivity analyses (not shown), assuming that heterogeneous variances may require modeling. The original power calculations were updated using actual data from the beginning of the trial. It was found that the average cluster size was 1.55 (SD = 1.39, ranging from 1 to 10 clusters and the total number of physicians was 92). The following assumptions were used in the power calculations: σ (population standard deviation) = 15 for SBP and 12 for DBP; α = 0.05, two-tailed; R = 0.9 (reliability); g = 2 (groups); n = 3 (waves, t = 0, 3 and 6 month); $s_{x}^{2}$(variance of time) = 0.125; inflation factor (IF) = 1+(clustersize-1)*ICC with clustersize = 1.55 and ICC = 0.01.

Thus, 100 subjects per group will provide 80% power to detect a 6 to 7 mm Hg differential change in SBP and a 5 to 6 mm Hg differential change in DBP, based on testing the Time (pre through post-intervention waves) × Group interaction in a mixed model, allowing for heterogeneous variances, serial correlations and modeling of design effects. As described below, analyses will be performed under an intent-to-treat design; therefore all patients, including those who drop out of the study will be invited back for the final assessments.

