### Mode of Intervention Delivery

The potential for low patient participation rates in the group classes and MINT counseling sessions is another real-world challenge encountered in this study. We have adopted several strategies to facilitate high participation rates, including offering classes in the clinic; determining a cohort's class schedule based on the most frequently selected time and date chosen by patients during the eligibility screen visit; and offering Saturday classes and make-up classes on an alternate day and time. Despite these efforts, approximately 50% of patients attend the weekly group classes, of which 35% have attended 9 to 10 of the classes (total of 10 classes). Most frequent reasons for low group class attendance include patients' reporting another time commitment or conflict, being too ill to travel to the classes on a weekly basis, inability to reach the patient to remind them of the class time and location, and patient's having difficulty arranging for paratransit services (e.g., Access-a-Ride) to bring them to the clinic on off hours (evenings and weekends).

Similarly, approximately 50% of patients have received the telephone-based MINT sessions to date. To increase the completion rate, Health Educators make four call attempts to each patient at different times of the day over a 2-week period before they are considered a missed appointment. However, it is often difficult to reach patients by phone as many participants have intermittent use of their phones and their numbers change frequently. Letters signed by the Health Educators are also sent to patients with the study coordinator's phone number. It is noteworthy that 47% of patients that attended at least 5 of the group sessions have completed at least 1 MINT session. Further, 42% of patients that attended no classes have completed at least 1 MINT session, which suggest that this intervention modality may be effective in certain subgroups.

Despite the many challenges we have experienced to date, implementation of this trial has presented us with the unique opportunity to question which intervention approaches work in real-world settings, where patients have competing priorities and the demands of life often outweigh the perceived benefits of participation. Based on our experiences implementing the TLC-Clinic trial, we would recommend future researchers conduct a formative evaluation prior to implementing the trial at the participating clinic sites.

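### An effect estimate and 95% CI are provided for only if the Group × Time test is significant, so a non-significant trial has no planned interval for SBP or DBP

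*Protocol article*

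**What the plan says.** The section Analysis of the Primary Aim first names the test: "The primary test concerns the Group × Time interaction, and the resulting F-test will provide the primary 'intent-to-treat' test of the hypothesis". SBP and DBP are to be examined separately, but "if the two variables are correlated, MANOVA will be used to test the hypothesis". The next step is estimation: "If this is statistically significant at the two-tailed α = 0.05 level, the magnitude of the treatment effect will be estimated", with a 95% CI, separately for SBP and DBP.

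That sentence is the article's only provision for an effect estimate or a confidence interval. The Abstract, Study Aims, Outcomes assessments and Sample Size and Power Analysis define the outcomes and the detectable differences. None of them says what will be estimated if the test is not significant.

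Two other places bear on the consequence. The Abstract gives the purpose: "This vanguard trial will provide information on how to refine MINT-TLC". The section Mode of Intervention Delivery reports that "approximately 50% of patients attend the weekly group classes".

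**The concern.** The primary outcome is a quantity, the change in SBP and DBP in mm Hg. Whether an F-test crosses 0.05 is no reason to estimate that quantity or to leave it unestimated. The interval matters most after a non-significant test, because it separates a trial that has excluded a useful effect from one that was too imprecise to tell. A p-value alone cannot do that.

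The form of the test sharpens the point. An interaction F-test over three waves, or a MANOVA on SBP and DBP together, has no direction and no mm Hg scale. If it is not significant and nothing else is planned, nothing interpretable remains on the hypothesised 6-month reduction.

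A non-significant result is realistic here by the article's own account of attendance. A trial meant to guide refinement and translation needs the size of the effect and its uncertainty in either case.

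**Working it through.** **Inputs**, all from Sample Size and Power Analysis:
- SD and alpha: "σ (population standard deviation) = 15 for SBP and 12 for DBP; α = 0.05, two-tailed".
- Follow-up spread: "the SD at follow-up will be as much as 25% larger in the MINT-TLC group". The upper limit is 1.25 × 15 = 18.75 for SBP and 1.25 × 12 = 15 for DBP.
- Correlation of baseline with follow-up: "will be 0.6 in the UC group and 0.4 in the MINT-TLC group".
- Clustering inflation: 1 + (1.55 − 1) × 0.01 = 1.0055.
- 100 per group, 80% power, detectable change of 6 to 7 mm Hg (SBP) and 5 to 6 mm Hg (DBP).

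**Step 1: reproduce the plan's figure.** Within an arm, Var(change) = s0² + s1² − 2·r·s0·s1.
- SBP, UC: 225 + 225 − 2(0.6)(15)(15) = 180, so SD 13.42.
- SBP, MINT-TLC: 225 + 351.56 − 2(0.4)(15)(18.75) = 351.56, so SD 18.75.
- SE (SBP) = √[(180 + 351.56)/100 × 1.0055] = 2.31 mm Hg.
- DBP in the same way: variances 115.2 and 225, SE 1.85 mm Hg.

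Detectable effect = (1.960 + 0.842) × SE = 6.48 (SBP) and 5.18 (DBP). Both lie inside the stated ranges, so the approximation is consistent with the plan.

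**Step 2: the chance of ending without a planned interval.** With a 1-df normal test, significance needs |estimate| > 1.96 × 2.31 ≈ 4.5 mm Hg for SBP. For a true effect d, power = Φ(d/SE − 1.96) + Φ(−d/SE − 1.96), and the chance of no planned interval is 1 − power. The last two columns give the mean of the estimates that pass the condition, E[estimate given |estimate/SE| > 1.96], and its ratio to the truth.

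| True SBP effect (mm Hg) | No planned interval | Mean estimate if significant | Ratio to truth |
|---|---|---|---|
| 7 | 14% | 7.61 | 1.09 |
| 6.48 (80% power) | 20% | 7.29 | 1.12 |
| 6 | 26% | 7.02 | 1.17 |
| 5.5 | 34% | 6.78 | 1.23 |
| 2.75 | 78% | 5.82 | 2.1 |

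The 5.5 row uses the SBP reduction that the Background quotes from the DASH study. The 2.75 row assumes that attendance of about 50% halves that effect; the article does not say so. For DBP, the chance of no planned interval is 20% at 5.18 mm Hg, with a mean significant estimate of 5.83 (ratio 1.12).

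**Step 3: sensitivity to the SD.** The 25% increase is an upper limit. With no increase and the same correlations, the MINT-TLC variance is 225 + 225 − 2(0.4)(225) = 270 and SE = √[(180 + 270)/100 × 1.0055] = 2.13. The chance of no planned interval is then 9% at 7, 14% at 6.48, 20% at 6 and 27% at 5.5 mm Hg. The mean excess at 5.5 is 17% instead of 23%.

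**Step 4: sensitivity to the form of the test.** The planned test may have more than one degree of freedom. Simulations placed each component at the 80%-power effect, except as noted:
- A 2-df interaction over three waves (assumed correlation 0.5, and a 3-month effect 70% of the 6-month effect): 73% power, ratio about 1.15.
- A joint SBP/DBP test (assumed correlation 0.6): 81% power, ratio about 1.11.

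**Step 5: what unconditional reporting gives.** Every trial reports an interval, with half-width 1.96 × SE: about ±4.5 mm Hg for SBP and ±3.6 mm Hg for DBP. The reported estimator is then unbiased across trials under this model.

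**The case against.** **The sentence says if, not only if.** It forbids nothing, the mixed model has to estimate the group differences in order to test them, and an unseen analysis plan may cover the null case. This stands as far as it goes: a prohibition would be an inference. But the article does more than stay silent. It writes a rule that attaches estimation to significance, and it offers no other provision. An analysis plan written to match would carry the condition forward.

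**A positive trial would report an exaggerated effect.** A reader might infer this from the last two columns of the table, but the documents do not support it for this trial. If the test is significant, the same estimate and CI appear with or without the condition, and the fix does not alter them. The ratios are averages over hypothetical significant trials. At the design effect about 62% of significant estimates exceed the truth, not all of them. The bias arises across trials, when only significant ones contribute an estimate.

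**The illustration is approximate.** This also stands. The SE uses the upper-limit SD, and a 1-df change-score test is not the planned F-test or MANOVA. The halved effect is weakly grounded: Mode of Intervention Delivery reports that 42% of those who attended no classes completed at least one MINT session, so no effect in non-attenders cannot be presumed. The rows at 6 to 7 mm Hg, the trial's own target, do not depend on that assumption.

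**Conclusion.** The point holds in this form: the article plans an estimate and 95% CI only for the case of a significant test, so a non-significant trial that follows it has no planned effect size or interval for SBP or DBP.

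Under the plan's upper-limit variances, a 1-df approximation and 100 per arm, that happens in about one trial in five even when the true SBP effect is the 6.5 mm Hg that gives 80% power. With no SD increase the chance at that effect is about 14%. Smaller true effects raise it. All these percentages are illustrative and are not exact properties of the planned test.

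The missing interval after a null result is the main harm. Average exaggeration across trials, about 12% at the design effect, is secondary and does not describe a single positive result. The stated sample size, alpha and power are not in question. The change should be made, since it costs almost nothing and lets the trial inform its own question whatever the outcome.

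**What to change.** Replace the conditional sentence in Analysis of the Primary Aim with:

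> The between-group difference in 6-month change in SBP and in DBP (MINT-TLC minus UC) will be estimated with 95% CI and reported whatever the result of the F-test or MANOVA.

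Any analysis plan should carry the same wording. The cost is one sentence: no extra data, patients or alpha, and the contrast comes from the mixed model already planned. Trial Status shows recruitment still open, so the change can be made before the final analysis.

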**Methods/Design:**

This randomized controlled trial tests the effectiveness of a practice-based comprehensive therapeutic lifestyle intervention, delivered through group-based counseling and motivational interviewing (MINT-TLC) versus Usual Care (UC) in 200 low-income, African Americans with uncontrolled hypertension. MINT-TLC is designed to help patients make appropriate lifestyle changes and develop skills to maintain these changes long-term. Patients in the MINT-TLC group attend 10 weekly group classes focused on healthy lifestyle changes (intensive phase); followed by 3 monthly individual motivational interviewing (MINT) sessions (maintenance phase). The intervention is delivered by trained research personnel with appropriate treatment fidelity procedures. Patients in the UC condition receive a single individual counseling session on healthy lifestyle changes and print versions of the intervention materials. The primary outcome is within-patient change in both systolic and diastolic BP from baseline to 6 months. In addition to BP control at 6 months, other secondary outcomes include changes in the following lifestyle behaviors from baseline to 6 months: a) physical activity, b) weight loss, c) number of daily servings of fruits and vegetables and d) 24-hour urinary sodium excretion.

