### Study Sites and Population

This study is being conducted within the Ambulatory Care Practice of the Bellevue Hospital Center (BHC), the largest comprehensive diagnostic center within the New York City Health and Hospitals Corporation. Approximately 20,000 patients receive treatment annually at BHC's adult medicine primary care practice, with just under 60,000 visits in 2009. To be eligible, patients must self-identify as black/African American, be at least 18 years old, currently receive care within the Ambulatory Care Practice and have had at least two appointments in the past year, have a diagnosis of HTN with uncontrolled BP on at least two visits in the past year (SBP ≥ 140 mmHg *or *DBP ≥ 90 mmHg or SBP ≥ 130 mmHg *or *DBP ≥ 80 mmHg for patients with diabetes or chronic kidney disease). In addition, all patients must have uncontrolled BP at the time of the consent visit, as measured by WatchBP (Microlife; Golden, CO), an oscilliometric validated BP monitor [40,41]. Patients are excluded if they are non-English speaking, participate in other HTN trials, have an arm circumference > 42 cm, have cognitive impairment based on the Comprehensive Assessment and Referral Evaluation Dementia Diagnostic Scale (CARE-DIAG) score ≥ 6 for patients age 60 and older,[42,43] are unwilling/unable to comply with the study protocol (either self-selected or by indicating that they could not complete all requested tasks including attending intervention classes if they were to be randomized to the MINT-TLC group), or unwilling/unable to provide informed consent. All patients who agree to take part in the study are asked to provide informed consent. The study was approved by the Institutional Review Boards of New York University and Bellevue Hospital Center. The study is monitored by a Data Safety Monitoring Board.

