### Chart Extraction Data

All patients have their medical records reviewed at baseline and at 6-months by study staff. Chart data extraction includes duration of HTN, evidence of target organ damage, changes in prescribed antihypertensive medications dosages (this reflects the intensity of treatment). Others include frequency of clinic visits and reasons for visits; and use of other medications that are known to affect BP such as NSAIDS and hormone replacement therapy. Patients in this population have comorbid illnesses, which may affect BP levels - the primary outcome of this study. As such, we will use the Charlson Comorbidity Index (CCI)[52] to adjust for both the confounding effects of comorbidity on BP and their non-uniform prognostic impact on patients. The CCI is a weighted index for prospectively classifying comorbid conditions, which takes into account the number and seriousness of comorbid diseases.

Data on *patient socio-demographic characteristics *are also collected for description of the cohort and to examine effects of these factors on BP control. Variables include age, gender, education level, income, marital status, employment status, and health insurance status.

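### The primary Group × Time test makes no use of the equal true baseline means that randomisation guarantees; it is valid, but gives up about 15–17% of the variance on the protocol's own assumptions

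*Protocol article*

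**What the plan says.** The Abstract defines the outcome: "The primary outcome is within-patient change in both systolic and diastolic BP from baseline to 6 months". Analysis of the Primary Aim names a mixed model in SAS PROC MIXED that includes everyone with at least one wave, and adds: "The primary test concerns the Group × Time interaction, and the resulting F-test will provide the primary 'intent-to-treat' test of the hypothesis". Sample Size and Power Analysis counts baseline among the response waves: "n = 3 (waves, t = 0, 3 and 6 month".

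On covariates, Analysis of the Primary Aim expects that randomisation and the absence of selection or attrition bias "will obviate the need for any covariates in the analysis". A fallback follows: "in the unlikely event that imbalances are identified, propensity score analyses or other methods will be used to condition on the covariates". It gives no threshold for imbalance and does not name baseline BP. Chart Extraction Data takes a different position: "we will use the Charlson Comorbidity Index (CCI)[52] to adjust for both the confounding effects of comorbidity on BP".

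The Randomization section places allocation after baseline data collection.

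**The concern.** With baseline as a response and a free mean for each arm at baseline, the 6-month Group × Time contrast is the difference between arms in mean change. Each arm's own baseline mean is subtracted in full, so the chance baseline difference enters the contrast with weight one. Since baseline precedes randomisation, that difference is pure noise. The best weight is the regression slope of follow-up on baseline, which is well below one at the correlations the article assumes.

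The article's stated reason for needing no covariates deals only with bias and imbalance. Randomisation does remove the need to adjust on those grounds. It does not remove the gain in precision from a baseline value that predicts the outcome. What is at stake is power, in a trial that names recruitment as one of its two main barriers.

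**Working it through.** **Inputs** (Sample Size and Power Analysis unless noted)
- Baseline SD: 15 mm Hg systolic (SBP), 12 diastolic (DBP).
- Follow-up SD: the same in usual care (UC); up to 25% larger in MINT-TLC (18.75 and 15).
- "the correlation between baseline and follow-up BPs will be 0.6 in the UC group and 0.4 in the MINT-TLC group".
- Cluster inflation: 1 + (1.55 − 1) × 0.01 = 1.0055.
- Two-sided α = 0.05 and 80% power: 1.960 + 0.842 = 2.802.
- Follow-up so far: 83% (Recruitment Challenges).

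Detectable difference = 2.802 × √(contrast variance × 1.0055). The calculation is for the 6-month contrast.

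**1. The plan's own figure.** Variance of change = SD₀² + SD₁² − 2ρ·SD₀·SD₁.
- UC: 225 + 225 − 2 × 0.6 × 225 = 180.0
- MINT-TLC: 225 + 351.6 − 2 × 0.4 × 15 × 18.75 = 351.6
- Sum 531.6; contrast variance at 100 per arm 5.316; detectable SBP difference 6.48 mm Hg.
- DBP scales by 12/15, giving 5.18 mm Hg.

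Both lie inside the stated ranges of 6 to 7 and 5 to 6 mm Hg. This is agreement with a range, by a change-score route. The article also lists R = 0.9 as a reliability. Read instead as the correlation between waves, it would give about 2.7 and 2.1 mm Hg, which does not fit the stated ranges.

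**2. Baseline-adjusted, complete data.** Common slope b = (0.6 + 0.4 × 1.25)/2 = 0.55. Residual variance = SD₁² + b²·SD₀² − 2b·cov.
- UC: 225 + 68.1 − 2 × 0.55 × 135 = 144.6
- MINT-TLC: 351.6 + 68.1 − 2 × 0.55 × 112.5 = 295.9
- Sum 440.4; ratio 440.4/531.6 = 0.829, a cut of 17.1%.

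A three-wave generalised least squares calculation, comparing a common with a free baseline mean and taking the 3-month SDs and correlations as equal to those at 6 months, gives the same 17.1%. Arm-specific slopes give 17.4%.

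| 100 per arm | Mean change | Adjusted |
|---|---|---|
| SBP detectable difference, mm Hg | 6.48 | 5.90 |
| DBP detectable difference, mm Hg | 5.18 | 4.72 |
| Power at 6.5 mm Hg SBP | 80.3% | 87.1% |

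Since 1/0.829 = 1.207, the unadjusted analysis needs about 21% more patients for the same power.

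**3. With 83% follow-up under the planned likelihood analysis.** Take 100 baselines and 83 follow-ups per arm, with dropouts contributing baseline only. Arm slopes are 0.6 (UC) and 0.5 (MINT-TLC). Conditional variances are 225 × (1 − 0.36) = 144.0 and 351.6 × (1 − 0.16) = 295.3.
- Free baseline means: 144.0/83 + (0.6 − 1)² × 225/100 + 295.3/83 + (0.5 − 1)² × 225/100 = 1.735 + 0.360 + 3.558 + 0.563 = 6.215. SBP 7.00, DBP 5.60 mm Hg.
- Common baseline mean: 1.735 + 3.558 + (0.5 − 0.6)² × 225/200 = 5.304. SBP 6.47, DBP 5.18 mm Hg.
- Ratio 5.304/6.215 = 0.853, a cut of about 15%.

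**4. Sensitivity.** With equal SDs and a single correlation ρ, the cut is (1 − ρ)/2: 20% at 0.6 and 30% at 0.4.

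**5. Where the loss comes from.** The variance of the baseline difference at 100 per arm is 2 × 225/100 = 4.5. The excess weight on it is 1 − 0.55 = 0.45, and 0.45² × 4.5 = 0.911. This is exactly the gap 5.316 − 4.404 from steps 1 and 2.

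**The case against.** The strongest reply is that the plan is coherent as it stands. The outcome is defined as change, the test matches it, the power statement is for that test, and the comparison is unbiased under randomisation. All of that stands: this is a precision point about a valid analysis.

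A second reply is that the article lists no fixed effects. A model with a common baseline mean also tests Group × Time, and parameterisation is commonly left to the statistical analysis plan, which is not shown. Free baseline means are indeed the ordinary reading and not written text; if the analysis plan already constrains the baseline, the efficiency point falls away. The article is not merely silent, though. It takes a position on covariates, for a reason that overlooks precision.

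Three stronger readings are tempting, and the document does not support them.
- *Covariates are ruled out.* They are not. The article states an expectation with an imbalance-triggered fallback, and elsewhere plans Charlson adjustment. The fallback still does not recover the precision, because it waits for observed imbalance and leaves the method open.
- *Attrition takes the trial outside its stated range and adjustment rescues it.* A completers-only change score with 83 per arm gives 7.11 mm Hg SBP (5.69 DBP), but the plan specifies full-information maximum likelihood. On that analysis SBP is about 7.00, at the upper edge of the stated range before any change, and DBP stays within 5 to 6.
- *Enrolment on raised BP adds a separate bias through regression to the mean.* The article requires that "all patients must have uncontrolled BP at the time of the consent visit", but this applies to both arms before allocation. The chance baseline difference has expectation zero, and step 5 shows that its variance is already the whole of the 17%.

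**Conclusion.** The point holds as a loss of precision. On the ordinary reading the primary contrast is a difference in mean change that ignores the known equality of the true baseline means. The avoidable variance is about 17% with complete data and about 15% at 83% follow-up under the planned likelihood analysis.

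These figures rest on the article's planning SDs and correlations, including an upper-bound 25% larger follow-up SD in MINT-TLC. With equal SDs the gain would be 20–30%. They also treat the covariance as known and, in the attrition case, assume that dropouts contribute baseline only. Type I error and unbiasedness are not in question.

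Separately, the article's two statements on covariates do not agree and need reconciling.

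**What to change.** In the same PROC MIXED model, constrain the arms to a common baseline mean: no group term at baseline, with group × month 3 and group × month 6 retained. Keep the heterogeneous variances, the clustering by physician and every patient with at least one wave. Make this the primary analysis regardless of any observed imbalance.

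Modelling only months 3 and 6 with baseline BP as a covariate is not an equal substitute here, because it drops patients who have baseline alone, contrary to the plan's inclusion rule.

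State also whether the Charlson index enters the primary model or a supporting analysis, so that Chart Extraction Data and Analysis of the Primary Aim agree.

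No new data are needed. The cost is a documented change: Trial Status reports 166 of about 200 patients already recruited, so the new primary model should be dated and recorded before any unblinded outcome analysis.

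### The terms named for correcting a baseline imbalance are constant over time, so they leave the primary Group × Time test unadjusted

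*Protocol article*

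**What the plan says.** All of the following is in the Protocol article. Under Analysis of the Primary Aim, "A mixed (fixed and random) effects model using SAS Proc Mixed is the method planned for use", and "The primary test concerns the Group × Time interaction". Baseline is one of the modelled waves: Sample Size and Power Analysis lists "α = 0.05, two-tailed; R = 0.9 (reliability); g = 2 (groups); n = 3 (waves, t = 0, 3 and 6 month".

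Randomisation and the absence of selection or attrition bias are expected to be such that they "will obviate the need for any covariates in the analysis". The fallback is that "in the unlikely event that imbalances are identified, propensity score analyses or other methods will be used to condition on the covariates". The next sentence states what goes into the model: "The predicted values of those analyses will be included as covariates together with the group by covariate interactions in the model". No covariate × time term is named.

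Separately, Chart Extraction Data says that a comorbidity index will be used to adjust for the effect of comorbidity on BP, without saying how it enters a model.

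**The concern.** The stated aim of the fallback is to condition on the imbalanced covariates. The test it has to serve is a difference between arms in change over time. A propensity value is a single number per patient. Alone, or multiplied by group, it moves all three of that patient's readings by the same amount, so it cannot act on a change.

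If the rule is followed as written and the imbalanced covariate predicts how BP changes, the imbalance still feeds into the primary estimate after the adjustment has been made.

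The trigger is realistic. With 100 per arm, the standard error of a standardised baseline difference is √(2/100) = 0.141. If eight independent covariates were compared at the 5% level (eight is my assumption), the chance of at least one flag is 1 − 0.95⁸ = 34%.

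**Working it through.** **Scale of the target.** Inputs from Sample Size and Power Analysis: SBP SD 15; follow-up SD up to 25% larger in MINT-TLC; baseline to follow-up correlation 0.6 (UC) and 0.4 (MINT-TLC); cluster inflation 1 + 0.55 × 0.01 = 1.0055; 100 per arm.

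- Variance of change, UC: 2 × 225 × (1 − 0.6) = 180.
- Variance of change, MINT-TLC: 225 + 351.56 − 2 × 0.4 × 1.25 × 225 = 351.56.
- SE of the difference: √(531.56 × 1.0055 / 100) = 2.31.
- Detectable at 80% power: 2.80 × 2.31 = 6.48 mm Hg.

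This agrees with the plan's 6 to 7 mm Hg. The same steps with SD 12 give 5.18 mm Hg for DBP, within its 5 to 6. The power statement is not in question; it supplies the yardstick.

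**Algebra.** Let patient i have group g and score p. The model as described is

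Y(t) = μ(t) + γg + δ(t)g + βp + θgp + error(t).

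The change from baseline to 6 months is

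Y(6) − Y(0) = [μ(6) − μ(0)] + [δ(6) − δ(0)]g + [error(6) − error(0)].

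βp and θgp have gone. Within an arm, the centred score is orthogonal to the time effects for any covariance matrix. With complete data, the Group × Time estimate and its SE are therefore exactly those of the model without the score.

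Now suppose that a covariate x shifts BP by λ(t) per SD, and the arms differ by Δ SD in x. The Group × Time estimate is then biased by Δ × [λ(6) − λ(0)]. Only the effect on change counts; a constant effect on level cancels.

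**Simulation.** True effect 0, 100 per arm, three waves, SD 15, correlation 0.6, unstructured covariance by maximum likelihood, 150 runs per row. Assumed imbalance 0.4 SD and 4 mm Hg of 6-month change per SD, so the expected bias is 1.6 mm Hg. The 17% missing mirrors the 83% retention reported under Recruitment Challenges. Entries are mean 6-month Group × Time estimates in mm Hg.

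| Data | No covariates | Score + group × score (as written) | Adding score × time |
|---|---|---|---|
| Complete | 1.575 | 1.575 | 0.008 |
| 17% missing at random | 1.492 | 1.486 | −0.051 |
| 17% missing, depending on the covariate | 1.429 | 1.460 | −0.021 |

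With complete data, the first two models differed by 0.00000 in every run and had the same mean SE (1.966). With missing data, single runs moved by 0.08 to 0.10 mm Hg on average (largest 0.42), but the bias stayed. Adding a physician random intercept (ICC 0.02), with time linear or categorical, did not change this.

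**If a group × covariate × time term is intended.** 1,000 complete-data simulations used the plan's variances, eight covariates in the score, an imbalance of 0.35 SD and 4 mm Hg per SD (expected bias 1.4 mm Hg).

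| Model | Mean estimate | SE |
|---|---|---|
| Unadjusted | 1.34 | 2.31 |
| Score × time only | −0.08 | 2.38 |
| Three-way, probability score centred at its mean | −0.08 | 2.39 |
| Three-way, logit score, at 0 | −0.07 | 2.39 |
| Three-way, probability score uncentred, at 0 | not used | 10.27 |

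The last row is 10.27 / 2.31 = 4.4 times the unadjusted SE, because the plain Group × Time coefficient then refers to a propensity of 0.

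**Range of the remaining bias** (Δ × effect on change): 0.1 × 2 = 0.2; 0.2 × 2 = 0.4; 0.35 × 4 = 1.4; 0.4 × 4 = 1.6 mm Hg. The upper end is demanding. An imbalance of 0.4 SD is 0.4 / 0.141 = 2.8 standard errors. An effect of 4 mm Hg per SD implies a correlation with change of 4/18.75 = 0.21 to 4/13.4 = 0.30.

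**The case against.** The best case on the other side is that this is a condensed article. It gives one sentence on terms, does not call the list complete, and allows other methods besides a propensity score; a covariate × time term could sit in the full plan. That lowers the weight of the point but does not remove it. The article chose to name the terms, and its next sentence sends the predicted values of whatever analyses are used into those same terms. Followed literally, it does not do what it says it is for.

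The branch is also contingent. The main intent-to-treat test is expected to be unadjusted, and across randomisations that test keeps its type I error. The bias here is conditional on a chance imbalance. This stands.

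Four stronger readings are tempting, and the documents do not support them:

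- A reader might infer that a faulty result would be reported as corrected. The article says nothing about how an adjusted result would be reported.
- A reader might infer that this is the only safeguard. Chart Extraction Data states another adjustment, for comorbidity, though its form is open and the same caution applies to it.
- A reader might infer that no interpretation conditions the test, or that a three-way model would lose a real effect. A three-way model with a centred or logit score removes the bias with an SE of 2.39. The collapse in precision needs an uncentred probability score read at 0, and the article fixes neither the scale nor the reference point.
- A reader might infer that any imbalance biases the result. Only one in a covariate that predicts change in BP does.

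**Conclusion.** The point holds in a limited form. The two terms named for conditioning on imbalanced covariates do not act on the primary test: exactly so with complete data, and very nearly so with about 17% missing.

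The consequence is moderate. Over the range 0.2 SD × 2 mm Hg to 0.4 SD × 4 mm Hg, the bias left is 0.4 to 1.6 mm Hg, or about 6% to 25% of the 6.48 mm Hg detectable SBP difference. Both factors are assumptions; the article gives neither. The conclusion that the terms are inert rests on algebra and does not depend on them.

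The sentence should be corrected before the adjusted analysis is run, because it specifies an adjustment that does not reach the test it is meant for.

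**What to change.** Replace the sentence on predicted values with wording to this effect:

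*Any baseline covariate used for adjustment, or the propensity score, enters the mixed model as a main effect and with a covariate × time interaction. Group × covariate and group × covariate × time terms are not part of the primary model; if they are examined, covariates are centred at the overall mean.*

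The same form should apply to the comorbidity index if it is used in the BP model. Entering covariates directly in place of a propensity score is optional.

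The cost is one sentence, no new data, and one degree of freedom per covariate with linear time or two with categorical time. With eight covariates in the score, the SE rose from 2.31 to 2.38, about 3%, and only when the adjustment is used. With two covariates it did not rise (1.966 to 1.935).
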